## Methods and Analysis

### Design

The TECAS trial is a multi-center, non-inferiority, randomized controlled trial and will be conducted simultaneously at five hospitals in China including The University of Hong Kong-Shenzhen Hospital; Guang’anmen Hospital of China Academy of Chinese Medical Sciences; Beijing First Hospital of integrated Chinese and Western Medicine; The First Hospital of Hebei Medical University; and Southwest Medical University, Hospital of Traditional Chinese Medicine. This study protocol is developed according to the Standard Protocol Items: Recommendations for Intervention Trials (SPIRIT) checklist (34) and has been approved by the Research Ethical Committee of The University of Hong Kong Shenzhen Hospital (HKU-SZH) (project approval number: 2019044; approved on 28 February, 2019), and all participating medical sites. The study protocol has been previously registered at ClinicalTrials.gov (NCT03909217). Figure 1 presents a study flow chart of the progress of patients through the trial.

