### Randomization

Patients will be randomly allocated (1:1) to groups receiving either escitalopram or TECAS. Stratified blocked randomization codes will be generated by PROC PLAN using SAS software, which will be stratified by the study site. The research assistants will use the randomization codes to produce opaque, sealed envelopes. Each envelope will be labeled with a participant-specific randomization identification number and contain a treatment allocation number. After the collection of patients’ basic information, participants will be assigned a randomization identification number by study staff. By using a central randomization system composed of free telephone, short message, and E-mail, the randomization identification number and treatment allocation will be accessed after participants received their baseline clinical evaluation. Participants, clinical psychiatrists, and treatment technicians will be aware of the treatment condition. The staff assessing treatment outcomes will be blinded to treatment condition because they will be segregated in a different clinic area. The participants’ treatment allocation will be required not to be discussed with these staff or other participants.

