### Outcomes

#### Primary Outcome

The primary outcome is clinical response at the end of treatment. The responder is defined as a ≥50% reduction from baseline MADRS at week 8. MADRS is a validated, self-reported and well-recognized questionnaire for depression (38–40). It consists of nine items, with the total range of 0–60 (higher scores indicate more severe condition). Previous research estimated the minimal clinically important difference (MCID) of MADRS to be 1.6–1.9 points changed from baseline (41).

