### Statistical Analysis

The proportion of participants with a reduction ≥50% in MADRS from baseline was 83.3% in the TECAS group and was 80.0% in the escitalopram group in our pilot study (unpublished data). Calculated by PROC POWER in SAS, in total, 470 participants will be needed to provide 90% power to detect a difference of −10% (the non-inferior margin) between groups in the proportion of participants with ≥50% in MADRS after 8 weeks of treatment at a 1-sided significance level of 5%, assuming a 20% loss to follow-up rate. The primary outcome will be evaluated based on the per-protocol (PP) population, defined as all randomized populations without major protocol violations. The primary outcome will be assessed using a 1-tailed test at a significance level of 0.025, while secondary outcomes using a 2-tailed test at a significant level of 0.05. For the proportion of participants with a reduction ≥50% in MADRS from baseline, the Cochran-Mantel-Haenszel test, stratified by site, will be used to test a hierarchical comparison between two groups. For the change from baseline in MADRS, the longitudinal data will be analyzed by fitting linear mixed-effects models using the baseline value as a covariate and treatment, visit, and treatment-by-visit interaction as fixed effects. The same approach will be used for the other continuous variables with longitudinal data, including HAMD-17, HAMA, PSQI, and SF-36. Missing data for the primary outcome will be imputed using the multiple imputation method under the missing at random assumption. For secondary outcomes, no imputation will be performed. To assess the robustness of the primary analyses, a sensitivity analysis will be performed without multiple imputation. All statistical analyses will be performed using SAS software, version 9.4 (SAS Institute).

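### The mixed models for the secondary continuous outcomes leave out site, the randomisation stratum that the primary analysis does use, so their standard errors will be slightly too large if sites differ

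*Protocol article*

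**What the plan says.** The Design section states that the trial "will be conducted simultaneously at five hospitals in China". Under Randomization, "Patients will be randomly allocated (1:1) to groups receiving either escitalopram or TECAS", using blocked codes "which will be stratified by the study site". Site is the only stratification factor named.

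The Statistical Analysis section treats the two kinds of outcome differently:

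- **Primary outcome (MADRS response at week 8):** "the Cochran-Mantel-Haenszel test, stratified by site, will be used to test a hierarchical comparison between two groups". Site is in this analysis and baseline MADRS is not. Baseline enters only through the endpoint definition: "The responder is defined as a ≥50% reduction from baseline MADRS at week 8".
- **MADRS change from baseline:** "fitting linear mixed-effects models using the baseline value as a covariate and treatment, visit, and treatment-by-visit interaction as fixed effects". The outcome's baseline value is in this model and site is not. The same section carries the approach over to HAMD-17, HAMA, PSQI and SF-36. No random effects or covariance structure are described.

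Secondary outcomes are tested two-sided at 0.05 without imputation. The only non-inferiority margin belongs to the primary outcome.

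**The concern.** When allocation is balanced within sites, the treatment difference is already protected from between-site variation. A model that ignores site does not recognise this. It counts the between-site variation as residual noise and reports a standard error larger than the true variability of the estimate.

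The plan also handles one scale in two ways: week-8 MADRS is analysed by site as a response and without site as a change score.

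Site differences are plausible. The hospitals are of different kinds, escitalopram is dosed flexibly by local psychiatrists, and the scales are administered by research assistants.

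What is at stake is modest: somewhat wide intervals and slightly low power for the secondary comparisons. It still deserves attention, because the Discussion wants to compare the treatments across several scales and on durability at follow-up. In that setting a difference that was missed is easily read as similarity.

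**Working it through.** **Inputs from the article.** Five sites; 1:1 allocation stratified by site; 470 randomised with 20% assumed loss, so 470 × 0.80 = 376 analysed, or 188 per arm. Pilot response "was 83.3% in the TECAS group and was 80.0% in the escitalopram group in our pilot study (unpublished data"; the trial is sized "to detect a difference of −10% (the non-inferior margin) between groups". The article gives no figure for site variance or for the baseline-response association, so there is no plan figure to reproduce on this point. Both are assumed below and shown as ranges.

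**1. Site omitted from a continuous-outcome model.** Let ρ be the site intraclass correlation after baseline adjustment, with residual variance scaled to 1.

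- With site in the model, the residual variance is 1 − ρ.
- Without site, the between-site part stays in. With S = 5 equal sites its expected contribution is about ρ(S − 1)/S = 0.8ρ, so the residual variance is about 1 − ρ + 0.8ρ = 1 − 0.2ρ.
- Ratio of reported standard errors, without to with site: √[(1 − 0.2ρ)/(1 − ρ)].
- If the true standard error is the one from the model with site, a nominal two-sided 5% test without site has actual size 2[1 − Φ(1.96 × ratio)].

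A simulation checks this. It uses one visit, 380 patients in 5 equal sites, exact balance within site, baseline as covariate and 3,000 runs.

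| ρ (assumed) | Formula ratio | Simulated SE without / with site | Simulated ratio | Size without site, formula | Size without site, simulated |
|---|---|---|---|---|---|
| 0.02 | √(0.996/0.98) = 1.008 | 0.0940 / 0.0932 | 1.009 | 4.8% | 4.5% |
| 0.05 | √(0.99/0.95) = 1.021 | 0.0936 / 0.0917 | 1.021 | 4.5% | 4.8% |
| 0.10 | √(0.98/0.90) = 1.043 | 0.0931 / 0.0893 | 1.043 | 4.1% | 4.2% |
| 0.20 | √(0.96/0.80) = 1.095 | 0.0921 / 0.0841 | 1.095 | 3.2% | 3.4% |

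At ρ = 0 both models give 0.0940. The Monte Carlo error of a simulated size is about √(0.05 × 0.95/3000) = 0.4 percentage points, so the small departures are not estimated sharply.

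The observed spread of the estimates across runs is the same with and without site (0.0937, 0.0930, 0.0892 and 0.0855 for the four rows, in both models). The omission therefore changes the reported precision, not the estimate's actual precision.

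**2. Baseline MADRS absent from the primary analysis.** From the planning rates, the standard error of the unadjusted risk difference is √[(0.80 × 0.20 + 0.833 × 0.167)/188] = √(0.2991/188) = 0.0399.

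A second simulation uses 188 per arm, baseline uniform from 12 to 30, response near 82% at mid-range, no treatment effect and no site effect. The log-odds slope per SD of baseline is assumed.

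| Slope per SD (assumed) | Unadjusted SE, model / observed | Adjusted SE, model | Variance removed |
|---|---|---|---|
| 0 | 0.0397 / 0.0400 | 0.0397 | about 0 |
| 0.2 | 0.0398 / 0.0391 | 0.0397 | 0.6% |
| 0.4 | 0.0403 / 0.0396 | 0.0399 | 2.4% |
| 0.6 | 0.0411 / 0.0412 | 0.0400 | 5.1% |

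The unadjusted standard error agrees with the observed one throughout. At the steepest slope, the planning half-width of 1.96 × 0.0399 = 7.8 percentage points would shrink to 7.8 × √(1 − 0.051) = 7.6, against a margin of 10.

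**The case against.** The best defence is that this is a condensed article. It calls the models mixed-effects but lists only the fixed effects, so a random site effect may sit in the full plan. That is possible. But the article gives a definite list of model terms, and it names site for the primary analysis immediately before. Taken as written, the list omits the stratum; if site is in the model in another form, one phrase would settle it.

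It can also be said that the error is small, conservative and confined to secondary outcomes. That stands and sets the weight of the point.

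A reader might infer three stronger things, none of which the article supports:

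- *That the non-inferiority conclusion is at risk.* The only margin applies to the primary outcome, whose test is already stratified by site. The secondary outcomes have no margin.
- *That the primary analysis is wrong because it ignores baseline MADRS.* Baseline is not a stratification factor. A site-stratified test without it is valid and its standard error already allows for chance imbalance. That response needs a fall of 6 points from a baseline of 12 and 15 points from 29 follows from the percentage definition and is not a flaw.
- *That leaving out site amounts to discarding patients.* With balance within site, the true variability of the estimate is the same either way. Only the reported standard error is inflated.

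**Conclusion.** The point holds for the secondary mixed models. As written, they omit the factor by which patients are randomised and by which the primary outcome is analysed. The reported standard errors of treatment differences would be too large by about 1%, 2% and 4% at assumed site intraclass correlations of 0.02, 0.05 and 0.10, and by about 10% at 0.20. If sites do not differ, nothing is lost.

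These figures assume one visit, equal-sized sites and exact balance within site. Dropout and unequal recruitment will make the real case less tidy, though the direction should be the same while allocation stays close to balanced within site. The primary non-inferiority test is unaffected.

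Adjusting the primary risk difference for baseline MADRS is a separate and optional gain of about 0 to 5% in variance over the slopes tried. It corrects no error.

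**What to change.** Add site as a fixed effect to the mixed model for each of MADRS change, HAMD-17, HAMA, PSQI and SF-36. If the full plan already includes site in another form, say so. With five sites this uses four degrees of freedom and needs no new data, only a change of wording made before unblinding.

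Optionally, pre-specify one supporting analysis of the primary outcome: the risk difference from a logistic model with treatment, site and baseline MADRS, standardised to the trial population and set against the same −10% margin. Keep the site-stratified Mantel-Haenszel analysis as primary. The cost is one more pre-specified analysis on data already collected.

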#### Secondary Outcomes

The secondary outcomes include (a) response rate based on HAMD-17. The responder is defined as the rate of a ≥50% reduction from baseline HAMD-17 at week 8; (b) remission rate, which is defined as a score of 12 or fewer points on the MADRS or as 7 or fewer points on the HAMD-17 at the end of treatment; (c) changes from baseline in the MADRS at week 2, 4, 8, and 12; (d) changes from baseline in the HAMA at week 2, 4, 8, and 12; (e) changes from baseline in the PSQI at week 2, 4, 8, and 12; (f) changes from baseline in the SF-36 at week 2, 4, 8, and 12; (g) changes from baseline in the HAMD-17 at week 2, 4, 8, and 12. HAMD-17 is a validated questionnaire that needs to be assessed by clinicians (42). The range of HAMD-17 is 0–52 (higher scores indicate more severe condition). HAMA is a validated 14-item scale for the measurements of psychic anxiety and somatic anxiety (43). Each item of HAMA ranges from 0 to 4, with a total range of 0–56. PSQI consists of 19 items, and is a reliable self-reported questionnaire for the measurement of sleep dysfunction (higher scores indicate more severe condition) (44). SF-36 is made up of 36 items grouped in 8 dimensions (45). This scale is used to assess the overall health status of patients. Figure 3 illustrates the SPIRIT diagram of assessments at enrollment, allocation, and different time points.

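### The mixed models for the secondary continuous outcomes use one baseline slope for all visits; adding baseline-by-visit is a minor improvement that costs almost nothing

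*Protocol article*

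**What the plan says.** The Secondary Outcomes section lists "changes from baseline in the MADRS at week 2, 4, 8, and 12", with the same four visits for HAMD-17, HAMA, PSQI and SF-36. For MADRS change, the Statistical Analysis section specifies "fitting linear mixed-effects models using the baseline value as a covariate and treatment, visit, and treatment-by-visit interaction as fixed effects". It continues: "The same approach will be used for the other continuous variables with longitudinal data, including HAMD-17, HAMA, PSQI, and SF-36". Four fixed effects are therefore named: baseline, treatment, visit and treatment-by-visit. On missing data it says "For secondary outcomes, no imputation will be performed", so the mixed model alone has to handle dropout for these outcomes.

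The primary outcome is handled separately. It is binary ("The responder is defined as a ≥50% reduction from baseline MADRS at week 8"), and for it "the Cochran-Mantel-Haenszel test, stratified by site, will be used", with multiple imputation.

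**The concern.** A single baseline term assumes that one extra point at entry predicts the same extra change at week 2 as at week 8. That is doubtful here. Entry MADRS runs from 12 to below 30 (Participants), and the pilot response rates were 83.3% and 80.0% (Statistical Analysis). To halve the score, a patient entering at 28 must fall 14 points and one entering at 14 must fall 7. If falls are roughly proportional to entry score, the slope of change on baseline follows the mean fall: shallow at week 2 and steep at week 8. A common slope is then a compromise that corrects too little at week 8.

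Two things are at stake for the week-8 comparison of the continuous scales. One is some avoidable loss of precision. The other is bias if the patients remaining in the two arms differ in baseline severity, because the model would correct that difference with the wrong slope. The setting leaves room for differing dropout: participants know their arm (Randomization), a twice-daily home device is compared with a tablet (Intervention Procedure), and 20% loss is planned.

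**Working it through.** **The plan's own figure.** There is none to reproduce. The document gives no SD, correlation, trajectory or power for any continuous outcome. The only sample-size figure, 470, belongs to the binary primary outcome and is used here just as N.

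**Inputs from the document.** N = 470, 1:1; visits at weeks 2, 4, 8 and 12; baseline MADRS 12 to below 30; 20% loss; MCID 1.6–1.9 (Primary Outcome).

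**Inputs assumed.** Residual SD 4/5/6.5/6.5 at the four visits; correlation about 0.7 between adjacent visits; unstructured covariance; no true treatment difference; about 20% missing at week 8. Three sets of slopes of change on baseline were tried.

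**Step 1: precision at week 8.** Simulated standard error of the treatment contrast, scaled to N = 470:

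| Assumed slopes, weeks 2/4/8/12 | SE, planned model | SE with baseline-by-visit | Ratio |
|---|---|---|---|
| −0.3/−0.4/−0.5/−0.5 (moderate) | 0.653 | 0.649 | 1.006 |
| −0.2/−0.4/−0.6/−0.65 (growing) | 0.664 | 0.648 | 1.025 |
| −0.1/−0.4/−0.8/−0.8 (strong) | 0.696 | 0.649 | 1.072 |

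**Step 2: closed-form check, complete data.** Let b be the vector of true slopes, Σ the residual covariance and Var(B) the baseline variance. The fitted common slope solves β = (1′V⁻¹b)/(1′V⁻¹1), with V = Σ + Var(B)(b − β1)(b − β1)′. The week-8 residual variance then rises by the fraction Var(B)(b₈ − β)²/σ₈². Take Var(B) = 16 (assumed), correlation 0.7 raised to the number of visits apart, and σ₈² = 6.5² = 42.25:

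- Moderate: β = −0.333; 16 × 0.167²/42.25 = 1.1% in variance, 0.5% in SE.
- Growing: β = −0.277; 16 × 0.323²/42.25 = 4.0% in variance, 2.0% in SE.
- Strong: β = −0.212; 16 × 0.588²/42.25 = 13.1% in variance, 6.3% in SE.

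This agrees with Step 1. A flat baseline distribution over 12–30 has variance 18²/12 = 27. The variance figures scale by 27/16, which gives SE increases of about 0.9%, 3.3% and 10.5%. In a separate simulation with mean falls of 22/45/68/64%, the SEs were 0.497 against 0.461 (uniform baseline, ratio 1.078) and 0.488 against 0.465 (bell-shaped baseline, ratio 1.049).

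**Step 3: bias at week 8.** The misfit enters the contrast through the slope error (b₈ − β) combined with the difference between arms in baseline among those still observed. Randomization makes that difference zero in expectation unless dropout acts differently in the two arms. With 1,000,000 simulated patients per scenario (Monte Carlo SE about 0.015) and the planned fixed effects:

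- Dropout related to baseline or to the last score alike in both arms: estimate within ±0.03, and the same with the interaction.
- Dropout rates differing by arm, or severity-related dropout in one arm only: about 0.05–0.3 points.
- Severe patients leaving one arm and mild patients the other: about 0.15 (moderate), 0.28 (growing) and 0.5 (strong) points.

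Adding baseline-by-visit with an unstructured covariance brought the bias to about zero throughout. A steeper stress case, with a dropout odds ratio of 2.7 per 5 baseline points in opposite directions by arm, gave 0.44–0.75 points under the planned model.

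**Step 4: false positives.** From 1,000 trials of N = 470 under no difference, two-sided 5%:

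| Dropout | Slopes | Planned model | With interaction |
|---|---|---|---|
| Severity-related, alike in both arms | growing | 5.5% | 5.3% |
| Severity-related, alike in both arms | strong | 5.5% | 4.9% |
| Opposite by arm | growing | 6.6% | 4.7% |
| Opposite by arm | strong | 11.8% | 4.3% |

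**The case against.** **Scope.** This is a condensed article, and the full protocol or SAP may hold a richer model. That is fair for the random effects and covariance, whose absence here is no finding. It is weaker for the fixed effects, which the article does state, naming one interaction and not the other. A single baseline covariate is also a conventional choice that contradicts nothing in the document. The point is therefore an improvement to a stated model and not the correction of an error.

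**The growing slope is conjecture.** A 50% cut-off defines a responder; it does not say that mean change is proportional to baseline. Selecting patients within a MADRS band can also produce regression to the mean, and so a baseline slope, as early as week 2. That would narrow the difference between visits. This stands: how far the slope grows is an assumption, and under the moderate set the loss is negligible.

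**The larger bias figures are stress cases.** Nothing in the document suggests that severe patients would leave one arm and mild patients the other. This also stands.

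**Other scales.** Only MADRS was simulated. Extending the change to HAMD-17, HAMA, PSQI and SF-36 rests on the plan's own decision to use the same approach for them, not on separate figures.

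**In the other direction,** the residual SD of 6.5 may be too large. With proportional falls of 60–65% it yields only 62–69% responders, below the pilot rates. Smaller SDs of about 4.5–5 with falls near 68% fit better, and the second simulation in Step 2 points to the upper part of the precision range.

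**Conclusion.** The point holds as a minor one. As written, the model has one baseline slope for four visits. If the baseline effect on change grows, week 8 is under-adjusted and its standard error is about 0.5–7% too large under the main assumptions. The upper end is not a strict bound: a flat baseline distribution combined with the strongest slopes gives about 10%. Bias requires dropout, or its relation to severity, to differ between arms. It is then mostly at or below 0.3 MADRS points and reaches about 0.5 or somewhat more only in opposite-direction stress cases, all below the quoted MCID of 1.6–1.9.

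Two stronger readings are tempting and are not supported. A reader might infer that severity-related dropout by itself biases the week-8 contrast. It does not, because under 1:1 randomization the misfit cancels when dropout acts alike in both arms. A reader might also infer that the non-inferiority conclusion is at risk because week 8 is the primary time point. The primary test uses binary response and does not pass through this model.

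**What to change.** In the Statistical Analysis section, list the fixed effects as baseline, treatment, visit, treatment-by-visit and baseline-by-visit, with an unstructured within-patient covariance. Apply this to MADRS and, by the same approach, to HAMD-17, HAMA, PSQI and SF-36. The covariance is worth naming together with the new term: under a random intercept alone, the interaction still left about 0.1 points of bias when dropout depended on the last observed score differently by arm.

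The cost is 3 degrees of freedom per model (four visits minus one) and one extra term in the SAS code, with no new data or patients. It should be specified before unblinding so that it cannot look data-driven.

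### HAMD-17 response and remission get no missing-data handling, so both rest on patients rated at week 8 and on a stronger assumption than the imputed primary outcome

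*Protocol article*

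**What the plan says.** All references are to the protocol article.

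- **Primary endpoint** (Primary Outcome): "The responder is defined as a ≥50% reduction from baseline MADRS at week 8".
- **Missing data, primary** (Statistical Analysis): "Missing data for the primary outcome will be imputed using the multiple imputation method under the missing at random assumption". A sensitivity analysis of the primary outcome without imputation is also planned.
- **Missing data, secondary** (same section): "For secondary outcomes, no imputation will be performed". The sentence makes no exception by type of outcome.
- **Binary secondary endpoints** (Secondary Outcomes): for HAMD-17 response, "The responder is defined as the rate of a ≥50% reduction from baseline HAMD-17 at week 8"; for remission, "a score of 12 or fewer points on the MADRS or as 7 or fewer points on the HAMD-17 at the end of treatment".
- **Models for secondary outcomes** (Statistical Analysis): a linear mixed model is given for change in MADRS, and "The same approach will be used for the other continuous variables with longitudinal data, including HAMD-17, HAMA, PSQI, and SF-36". No model is named for the two binary secondary endpoints.
- **Population** (same section): the primary outcome is evaluated in the "per-protocol (PP) population, defined as all randomized populations without major protocol violations". No population is named for the secondary outcomes.
- **Visits** (Intervention Procedure): MADRS and HAMD-17 are both rated at baseline and at weeks 2, 4, 8 and 12.
- **Loss** (Statistical Analysis): 20% overall; no figure by arm.

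**The concern.** For the continuous outcomes, leaving missing values unimputed does little harm. A mixed model uses the week-2 and week-4 scores of a patient with no week-8 score and is valid under missing at random.

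That protection does not reach the two binary endpoints, which are each read at one visit. Under the stated rule, a patient without a week-8 rating has no value and leaves the denominator. Counting such a patient as a failure would itself be an imputation, which the sentence rules out.

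The plan then makes two different assumptions about the same missed visit. For MADRS response it lets missingness depend on observed data. For HAMD-17 response and remission it needs missingness to be unrelated to outcome within arm. If patients with poor early scores are more often absent at week 8, the first assumption can hold while the second fails. Remission shows this most clearly, since half of its definition uses the week-8 MADRS that the primary analysis imputes.

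At stake are the level of two clinically prominent rates, possibly their between-arm difference, and how far they can be compared with the primary result.

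**Working it through.** **1. Patients affected.** The inputs are N = 470, 1:1 allocation (235 per arm) and 20% loss, all from the article.

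- Without week-8 data: 470 × 0.20 = 94.
- Observed: 470 × 0.80 = 376, or 188 per arm if loss is equal.

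94 is an upper figure for the mismatch with the primary analysis. Any of these patients whom the per-protocol definition excludes are absent from the primary analysis too.

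The 470 is taken as given. With the stated pilot rates (83.3% and 80.0%), 10-point margin, 90% power and one-sided 5%, the usual unpooled formula gives 145 per arm, 290 in total, and 290 / 0.8 = 363 after loss, so 470 is not reproduced. That is a separate matter, and nothing below depends on it.

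**2. Bias in the reported rate within an arm.** Let p be the response rate in those observed, q the rate that those lost would have had, and d the proportion lost. The available-case analysis reports p. The rate in all patients is (1 − d)p + dq. The overstatement is d(p − q).

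Assumed: p = 80%, q = 40% or 60%. Neither value of q is in the article; p is close to its pilot rates.

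| q | d | Rate in all patients | Reported | Overstatement |
|---|---|---|---|---|
| 40% | 20% | 0.80 × 0.80 + 0.20 × 0.40 = 72% | 80% | 8 points |
| 60% | 20% | 0.80 × 0.80 + 0.20 × 0.60 = 76% | 80% | 4 points |

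**3. Bias in the between-arm difference.** With the same p and q in both arms, the reported difference is 0 and the difference in all patients is −(d_T − d_C)(p − q), where T is TECAS and C is escitalopram.

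- Equal loss, 20% and 20%: (0.20 − 0.20)(p − q) = 0, so no bias.
- 25% on TECAS and 15% on escitalopram (assumed; still 20% overall), q = 40%: 0.75 × 0.80 + 0.25 × 0.40 = 70% against 0.85 × 0.80 + 0.15 × 0.40 = 74%. The difference is −4 points, reported as 0.
- Same split, q = 60%: 0.60 + 0.15 = 75% against 0.68 + 0.09 = 77%. The difference is −2 points, reported as 0.
- With the split reversed, the signs reverse.

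**4. Scale.** With 188 observed per arm at 80%, the standard error of the difference is √(2 × 0.80 × 0.20 / 188) = 0.041. A 2-4 point bias is therefore about half to one standard error.

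Steps 2 and 3 compare the available-case figure with the rate in all patients. Imputation under missing at random would recover only the part of that gap that the observed scores explain.

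**The case against.** **The primary analysis is per-protocol.** The article does not say whether stopping treatment is a major violation. A reader might infer that someone who quits at week 4 for lack of effect is kept in MADRS response and dropped from remission. The text does not establish that, since this patient may be excluded from both. This stands, and it is why 94 is an upper figure. But imputing the primary outcome serves a purpose only if some patients without week-8 data remain in the per-protocol set.

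**Withdrawal is not the same as a missing rating.** A patient who stops treatment but is rated at week 8 counts in all three endpoints. The planned 20% is loss to follow-up for any reason, not loss for lack of effect. This stands. The issue is confined to missing week-8 ratings.

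**A matching analysis already exists.** The unimputed MADRS sensitivity analysis can be set beside HAMD-17 response, and the mixed models give a week-8 contrast on both scales that is valid under missing at random. This limits the gap to two dichotomised endpoints. It does not close it, because the sensitivity analysis matches the endpoints only on the weaker, available-case basis.

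**The statistical analysis plan may settle it.** A likelihood-based model for repeated binary data also imputes nothing, and the article names no method for these endpoints. That is possible, but the article fixes a blanket rule and restricts its likelihood-based models to continuous outcomes. Available-case analysis is the natural reading.

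**Unequal loss is conjecture.** A twice-daily home device and a tablet, both given unblinded, could lose patients at different rates, but the article gives no evidence that they will. This stands.

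**Conclusion.** The point holds as a limited one. The stated rule leaves HAMD-17 response and remission to patients with a week-8 rating, on a stronger missingness assumption than the primary analysis makes for the same visit.

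Up to about 94 of 470 patients are affected. Under the assumed rates, each arm's rate is overstated by 4-8 points at 20% loss. The between-arm difference is unbiased if loss is equal and off by 2-4 points at 25% versus 15%. The response among those lost and the split by arm are assumptions.

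A reader might infer that the non-inferiority conclusion is at risk, or might measure the 2-4 points against the 10-point margin. The documents support neither. The primary outcome is imputed and its test is untouched. The margin belongs to the primary outcome only, while secondary outcomes are tested two-sided at 0.05. Nor does the Discussion make HAMD-17 response a condition for the primary claim; it gives HAMD-17 a supporting role in judging severity. Two of the seven listed secondary outcomes are concerned. The change is still worth making, because it is cheap and removes an inconsistency.

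**What to change.** In the Statistical Analysis section, limit the no-imputation sentence to the continuous secondary outcomes and add a rule for the binary ones:

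- Impute the week-8 MADRS and HAMD-17 total scores (not responder status) by multiple imputation under missing at random, using the baseline, week-2 and week-4 values of both scales, by arm.
- Derive HAMD-17 response and remission from the imputed scores in each completed data set, in the same analysis population as the primary outcome, and pool across imputations.
- Report the available-case version of both endpoints as a sensitivity analysis, as is already planned for the primary outcome.
- Keep the mixed models for continuous outcomes without imputation.

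The change should be made before outcome data are examined by arm. It costs a short text amendment, a slightly larger imputation model and a little more analysis work. It needs no new visits, data or patients.
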